#### Secondary outcomes

Secondary outcomes will include diaphragmatic function, respiratory parameters, clinical outcomes, and quality of life.

Diaphragm function will be evaluated using a portable ultrasound device (SII, Sonosound Medical Devices Co., Ltd.). Diaphragm excursion will be measured using M-mode ultrasound. Patients will be positioned semi-recumbently, and a trained sonographer will use a convex-array probe placed at the mid-axillary line beneath the right costal margin to obtain the maximal diaphragm excursion during quiet breathing. Each measurement will be repeated three times and averaged. Diaphragm thickness will be measured with B-mode ultrasound using a high-frequency linear-array probe placed along the anterior axillary line at the 8th to 9th intercostal space, the thickness will be assessed at end-expiration and end-inspiration. All measurements will be performed at baseline (pre-intervention) and after 3 weeks of intervention.

Respiratory parameters, including MIP, forced vital capacity (FVC), peak expiratory flow (PEF), and forced expiratory volume in one second (FEV1), will be assessed using a portable spirometer (X1, Seck Medical Devices Co., Ltd., Xiamen, China). The tracheostomy cuff is inflated to 25 cmH₂O with patients in a semi-recumbent position (45°). For MIP assessment, patients will perform five maximal inspiratory efforts from end-expiratory volume, with the highest value being recorded from three reproducible trials, each demonstrating <10% variation. For spirometric parameters (FVC/PEF/FEV1), patients will perform three forced expiratory maneuvers from total lung capacity with ≥30 s rests between trials, adhering to ATS/ERS standards. Specifically, FVC will use the highest value from ≥2 reproducible trials (<5% variation), PEF will take the highest peak flow from any valid trial, and FEV1 will use the highest value from ≥2 trials with acceptable start-of-test criteria. All measurements will be performed at baseline (pre-intervention) and after 3 weeks of intervention.

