### Statistical analysis

The effect of the intervention will be evaluated based on both intention-to-treat (ITT) and per-protocol (PP) principles. Between-group comparisons for the primary outcome (decannulation success rate) will be conducted using the chi-square test or Fisher’s exact test, along with calculation of relative risk (RR), absolute risk reduction (ARR), and number needed to treat (NNT). Multivariate logistic regression analysis will be used to adjust for prespecified covariates such as age, sex, and stroke type. Between-group comparisons for continuous secondary outcomes will be conducted using t-tests or Mann–Whitney U tests. Repeated measures data will be analyzed using mixed linear models. Categorical secondary outcomes will be analyzed using the same approach as for the primary outcome. Time-to-event outcomes will be analyzed using Kaplan–Meier survival analysis and Cox proportional hazards regression models.

Missing data will primarily be handled using mixed-effects models under the missing at random (MAR) assumption, with multiple imputation and complete case analysis conducted as sensitivity analyses. Prespecified subgroup analyses will include factors such as stroke type and age, with effect heterogeneity evaluated using interaction terms and controlled for multiple comparisons via the Benjamini-Hochberg method. Sensitivity analyses will also include comparisons between ITT and PP outcomes, comparisons of different statistical methods, and assessment of covariate selection strategies.

All analyses will be performed using R software (version 4.2.0), employing two-sided tests with a significance level of 0.05. The analysis will be conducted by an independent statistician, and the analysis plan was pre-specified before enrollment of the first patient to ensure reproducibility and transparency. Categorical variables will be presented as frequencies (percentages), and group comparisons will be conducted using the chi-square test or Fisher’s exact test. Continuous variables will be presented as mean ± standard deviation or median (interquartile range), depending on distributional characteristics. Group comparisons will be conducted using the t-test or Mann–Whitney U test. Safety analyses will include the incidence of adverse events and between-group comparisons.

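### The main analysis is not identified for MIP, FVC, PEF, FEV1 and the diaphragm measures; a single baseline-adjusted model should be named

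*Protocol article*

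**What the plan says.** Three statements in the protocol article bear on this point.

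- **Statistical analysis, comparison of groups:** "Between-group comparisons for continuous secondary outcomes will be conducted using t-tests", with the Mann–Whitney U test as the alternative. The choice between t-test and Mann–Whitney is repeated near the end of the section, after a sentence that makes the summary statistics depend on the observed distribution.
- **Statistical analysis, next sentence:** "Repeated measures data will be analyzed using mixed linear models". The outcomes that count as repeated measures are not listed.
- **Secondary outcomes:** the respiratory set is given as "Respiratory parameters, including MIP, forced vital capacity (FVC), peak expiratory flow (PEF), and forced expiratory volume in one second (FEV1"), and for both this set and the diaphragm ultrasound measures the text says "All measurements will be performed at baseline (pre-intervention) and after 3 weeks of intervention". Table 1 agrees, with ticks at V1 and V4 only. The weekly MIP readings described for the training arm serve to set the training load and are not in the outcome schedule.

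The questionnaires (EQ-5D-5L, Borg, HADS) differ, because they have a baseline and two later visits, at week 3 and 3 months. The only covariate adjustment that the section describes is for a binary outcome: "Multivariate logistic regression analysis will be used to adjust for prespecified covariates such as age, sex, and stroke type". Randomisation is stratified by age (at or below 40 years against above 40) and stroke type.

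**The concern.** For each two-time-point outcome, the text allows an unadjusted two-sample test or a mixed model and does not say which result is the main one. It also does not say whether the two-sample test is applied to week-3 values or to change from baseline. These choices give different estimates, standard errors and p-values from the same data.

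If the two-sample test is the main analysis, it uses the baseline inefficiently (change scores) or not at all (week-3 values), and it ignores both stratification factors. With 30 per arm, chance differences in baseline MIP or FVC are to be expected, and part of any such difference would pass into the estimated treatment effect. The outcomes are labelled secondary, but the Introduction places respiratory function and respiratory muscle strength within the trial's aim and hypothesis, so the precision of these comparisons matters to what the trial can say.

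**Working it through.** **The plan's own figure.** There is none to reproduce. The sample size calculation covers only the binary primary outcome.

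**Inputs from the document.** 30 per arm randomised; 26 per arm before inflation for 15% attrition; two-sided significance level 0.05; one baseline and one week-3 value per outcome.

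**Inputs assumed.** A true difference d = 0.6 SD, and a baseline to week-3 correlation r of 0.3 to 0.7. The document gives neither. The SD is taken as equal at the two times.

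**Variance of the treatment estimate, relative to a t-test on week-3 values.**

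- Week-3 t-test: 1
- Change-score t-test: 2(1 − r)
- ANCOVA on the baseline value: 1 − r²

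**Power, normal approximation.** Power = Φ(d·√(n/2) / √(variance factor) − 1.96).

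With n = 30, d·√(n/2) = 0.6 × √15 = 2.324. The week-3 t-test has Φ(2.324 − 1.96) = Φ(0.364) = 64%.

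| r | 1 − r² | ANCOVA power | 2(1 − r) | Change-score power |
|---|---|---|---|---|
| 0.3 | 0.91 | Φ(2.436 − 1.96) = 68% | 1.40 | Φ(1.964 − 1.96) = 50% |
| 0.5 | 0.75 | Φ(2.683 − 1.96) = 77% | 1.00 | Φ(2.324 − 1.96) = 64% |
| 0.6 | 0.64 | Φ(2.905 − 1.96) = 83% | 0.80 | Φ(2.598 − 1.96) = 74% |
| 0.7 | 0.51 | Φ(3.254 − 1.96) = 90% | 0.60 | Φ(3.000 − 1.96) = 85% |

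With n = 26, d·√(n/2) = 0.6 × √13 = 2.163. The week-3 t-test has Φ(0.203) = 58%. ANCOVA has 70%, 77% and 86% at r = 0.5, 0.6 and 0.7. Exact noncentral-t values are one to two points lower throughout, which does not alter the comparison.

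**Equivalent sample size.** 30/(1 − r²) gives 33, 40, 47 and 59 per arm at r = 0.3, 0.5, 0.6 and 0.7. These are the arm sizes at which an unadjusted week-3 test would match ANCOVA with 30.

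**Chance imbalance.** The standard error of the baseline difference is √(2/30) = 0.258 SD. A gap larger than 0.25 SD in either direction has probability 2 × [1 − Φ(0.25/0.258)] = 0.33. A week-3 comparison carries about r times the gap: at r = 0.6, a gap of 0.25 SD shifts the estimate by 0.6 × 0.25 = 0.15 SD.

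**The mixed-model reading.** With two time points and complete data, a mixed model that treats baseline as an outcome with unconstrained group means estimates the same quantity as the difference in mean change. One that has baseline as a covariate, or constrains the group means to be equal at baseline, behaves like ANCOVA. So even if that sentence covers MIP and the others, the precision depends on a form that the article does not give.

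**The case against.** A reader might infer that the plan throws the baseline away and so gives up the whole step from 64% to between 77% and 90% power. The documents do not support that.

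- The mixed-model sentence follows directly, and baseline plus week 3 can be read as repeated measures. The t-test sentence has a natural use for an outcome with no baseline, such as length of stay. This stands: both readings are open, and the text supports an unidentified main analysis rather than a discarded baseline.
- The two-sample test might be on change. At r = 0.7 the gain from ANCOVA is then about 5 points (85% to 90%), not 26. This stands.
- Both r and the 0.6 SD effect are assumed. At r = 0.3 ANCOVA adds only about 4 points to a week-3 test (64% to 68%). This stands.
- An article commonly leaves model detail to the analysis plan, which the article says was fixed before enrolment and which is not shown. The section also states "Missing data will primarily be handled using mixed-effects models under the missing at random (MAR) assumption" and lists as sensitivity analyses "comparisons of different statistical methods, and assessment of covariate selection strategies". This stands only in part. An unlisted covariate would be no finding by itself, but here the article names a test for these outcomes twice and places a second method beside it without ranking them.

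A reader might also infer bias. Under randomisation the unadjusted test remains valid; what is lost is precision. Finally, these are secondary outcomes in a trial that its Discussion calls exploratory.

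**Conclusion.** The concern holds in a limited form. The Statistical analysis section allows two methods for MIP, FVC, PEF, FEV1 and the diaphragm measures and does not say which is the main one. If it is the t-test or Mann–Whitney test, the analysis is less precise than one adjusted for a baseline that will be collected anyway.

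The size depends on assumptions outside the document. For a 0.6 SD effect with 30 per arm, ANCOVA gains 4 to 26 points of power over a week-3 t-test for r from 0.3 to 0.7, and about 13, 9 and 5 points over a change-score test at r = 0.5, 0.6 and 0.7. If the main analysis turns out to be a mixed model with baseline as covariate or constrained, nothing is lost and only the wording needs repair. There is no bias and no effect on the decannulation comparison. The change is worth making because it needs no new data and removes a choice between competing results.

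**What to change.** In the analysis plan, and in the protocol text if it is amended:

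1. Name one main analysis for MIP, FVC, PEF, FEV1, diaphragm excursion and diaphragm thickness: a linear model of the week-3 value on treatment, baseline value, age stratum and stroke type. Report the adjusted mean difference with its 95% confidence interval.
2. For EQ-5D-5L, Borg and HADS, use the mixed model on week 3 and 3 months, with baseline as covariate, visit, treatment and treatment-by-visit.
3. Keep the t-test and Mann–Whitney test as sensitivity analyses and for outcomes without a baseline, such as length of stay. State whether any such sensitivity test uses week-3 values or change.

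The cost is a few sentences, minor programming and a few degrees of freedom. Sample size and visit schedule are unchanged.

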### Ethics and dissemination

This study was reviewed and approved by the Medical Ethics Committee of Guangdong Sanjiu Brain Hospital (approval no. 2025-01-006), and was registered with the Chinese Clinical Trial Registry (registration no. ChiCTR2500097604). Throughout the study, the ethical principles of the Declaration of Helsinki and the relevant regulations outlined in the Measures for the Ethical Review of Biomedical Research Involving Human Subjects will be strictly adhered to.

At enrollment, all participants or their legal representatives provided written informed consent before participating in the study. During the informed consent process, the investigators clearly explained the study’s purpose, procedures and potential risks and benefits to the participants. It was specifically emphasized that participation was entirely voluntary, and participants retained the right to withdraw at any stage without prejudice to their access to standard medical care. To facilitate participant withdrawal, a simplified procedure was implemented, requiring only verbal or written notification to the investigators. The informed consent form was written in plain language and sufficient time was provided for patients and their families to ask questions and consider relevant matters. All medical procedures and testing costs related to the study were covered, ensuring no additional financial burden for the patients. Participants were also informed that, in the event of a study-related adverse event, appropriate compensation and medical treatment would be provided.

The results of this study will be submitted to peer-reviewed journals in accordance with the publication standards of the International Committee of Medical Journal Editors (ICMJE) and the CONSORT statement, to ensure transparency in the research process and outcomes. Provided that participant privacy is fully protected, the study data will be made openly accessible to the academic community via a secure platform, in accordance with relevant protocols, to promote scientific exchange and further research.

## Discussion

Rehabilitation of respiratory function in post-stroke patients with tracheostomy has been a key focus of clinical research. Previous studies (15, 16) have confirmed that IMT can improve respiratory muscle function and strength, enhance cough efficiency, and promote pulmonary function recovery. However, traditional IMT methods have several limitations. For example, threshold loading devices lack flexibility and cannot adjust loading intensity based on the patient’s lung volume (20); they lack real-time feedback mechanisms, which affects patient compliance (21); existing protocols insufficiently account for the specific pathophysiological characteristics of patients with neuromuscular disorders (22); and most traditional IMT devices use fixed resistance, making it difficult to accommodate the dynamic demands of the respiratory cycle (23). Currently, most studies on TFRL-IMT focus on mechanically ventilated or COPD populations, with relatively few systematic investigations in post-stroke tracheostomy patients. Therefore, this study designed a randomized controlled trial to evaluate the effects of TFRL-IMT on respiratory function in post-stroke tracheostomy patients.

This study will adopt a single-centre, assessor-blinded, parallel-group randomized controlled design, with stratified block randomization used to control for confounding variables such as age and stroke type. The TFRL-IMT technique is innovative in providing a flow resistance load that decreases progressively with increasing lung volume, thereby ensuring balanced load distribution throughout the respiratory cycle (24, 25). A key strength of the study design is the establishment of a comprehensive assessment system including objective physiological indicators, clinical outcomes, and quality of life measures. The electronic training device employed in the study featured real-time data feedback, which can accurately quantify the training parameters and improve patient training compliance (25). To accommodate the characteristics of this specific population of post-stroke tracheostomy patients, the training load was dynamically adjusted based on the patient’s actual MIP percentage, thereby addressing the shortcomings of traditional methods in individualized design. Additionally, the study systematized the decannulation decision-making process and used a blinded assessment design to reduce assessment bias, thereby providing high-quality evidence for respiratory rehabilitation in post-stroke tracheostomy patients.

This study considers the potential mechanisms by which TFRL-IMT improves clinical outcomes as follows. The electronically controlled resistance valve system delivers a flow resistance load that varies with lung volume and conforms to the pressure–volume relationship of the respiratory muscles (24, 25), thereby optimizing the training load, which ensures that the respiratory muscles receive appropriate stimulation at different levels of lung volume, and inducing comprehensive neuromuscular adaptations (23, 29). Compared with traditional methods, TFRL-IMT enables greater lung volume expansion and higher inspiratory flow rates at the same training intensity (23), thereby enhancing tolerance to higher training loads and increasing the total workload (25). This physiological advantage facilitates the enlargement of respiratory muscle fiber cross-sectional area (30) and improvement in oxidative capacity (31), thereby strengthening overall respiratory muscle function. Moreover, load parameters scientifically set according to respiratory physiology principles (30% of MIP) induce adaptive changes in respiratory muscles while minimizing the risk of overfatigue (32). From a neurophysiological perspective, regular inspiratory muscle training can reshape the central nervous system’s control mode of the respiratory muscles (33, 34), enhance motor unit recruitment efficiency (35, 36), and contribute to the reconstruction of respiratory neural circuits after stroke (37). Furthermore, enhanced diaphragm function improves alveolar ventilation and enhances coughing ability and reduces the risk of infection (38), while the optimisation of oxygenation status brought about by improved respiratory function can reduce the inflammatory response, which in turn indirectly promotes neurological function recovery (39).

This study has several limitations. First, the generalisability of the findings is limited by the single-centre design. Second, the relatively short follow-up period (3 months) may not be sufficient to fully evaluate the long-term effects of the intervention. Additionally, this study relied on specific electronic devices during implementation, which may somewhat limit the dissemination and application of the study methodology to primary medical institutions or resource-limited areas. Although strict inclusion and exclusion criteria were applied, the highly heterogeneity of stroke patients—including varied comorbidities, stroke types, and severity—may result in diverse patterns of respiratory dysfunction, potentially affecting the generalisability of the findings.

This study protocol outlines the design of an exploratory randomized controlled trial evaluating a novel, electronically controlled TFRL-IMT approach in post-stroke tracheostomy patients. If proven effective, this intervention could serve as a valuable adjunct to standard rehabilitation by enhancing respiratory muscle function to facilitate decannulation. The findings will provide high-quality evidence to guide respiratory rehabilitation strategies in this vulnerable population. Furthermore, the standardized protocol may support future multi-center studies and personalized training programs. A comprehensive assessment of physiological, clinical, and patient-reported outcomes will offer a holistic understanding of the intervention’s impact.
